**Methods and analysis:**

The *Good Start in Life* study will use a quasi-experimental design (with a matched control geographical area) consisting of a combination of interventions that will build multisectoral collaboration across education, health and social services that connect and support families with children from birth to 5 years. The control area will be matched on demographic characteristics and early child development outcomes and trends over the pre-intervention period. Evaluation data will be collected at baseline, and then on an annual basis for a further three years. A mixed methods approach will be used to evaluate delivery processes: quantitative (checklists, questionnaires) and qualitative methods (observations, focus groups and key stakeholder interviews). Effectiveness of the programme will be evaluated by comparing early child development outcomes between the comparator areas from the Australian Early Development Census in 2024. The primary focus will be on reducing the number of children who are developmentally vulnerable on at least one early development index (EDI). Separate tests will be conducted for significant differences in the percentage of children at risk in each of the five individual EDI domains. These domains are physical health and wellbeing, social competence, emotional maturity, language and cognitive skills, and communication and general knowledge.

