Literature on integration between early childhood centres reports that improving collaboration between services by creating more connected and productive early childhood programmes and networks provides better opportunities for positive outcomes for children and families [14]. Further studies have shown that the creation of a “virtual” network in which services do not need to relocate to a singular location produces the same benefits as co-located services [15].

As the nature of service integration prohibits a singular definition, a fit-for-purpose, context-and cultural- specific definition needs to be developed. In this project, the development of a definition will be considered as an outcome as this is an iterative process and will be refined throughout the project to represent the context, nature, and function of the integrated network most accurately. Broadly, this project views service integration as the creation of or strengthening of agency between early childhood services and programs across sectors within the local area. Such integration should provide a more comprehensive connection for families and greater numbers and quality of developmental opportunities for children, leading to better outcomes.

This project aims to evaluate an intervention designed to integrate child and family services within the district and embed allied health programs into early childhood education and care services and playgroups and to evaluate the outcomes and processes of the intervention. The Project Management Team (PMT) collaborate with local services to form a network of related services for children aged between birth and 5 years across the health, education, and social services sectors, allowing families to more easily access and navigate through different services.

The two main aims for this project are:

To create an integrated network of services for young children and families in target suburbs in the Belconnen district in the ACT.To reduce the proportion of developmentally vulnerable children in the target suburbs of the Belconnen district in the ACT.

The following questions will be addressed:

Does a multi-sector, multi-component approach reduce the proportion of children who are considered developmentally at risk in the intervention community compared to the control community?What is the reach, participation, intervention quality and dose of the interventions delivered and what were the barriers to, and facilitators of, implementation?

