#### Developmental vulnerability

The primary aim, to reduce the proportion of children who are developmentally vulnerable, will be measured by comparing results from the AEDC. A baseline measurement was recorded using the 2018 AEDC data for each intervention suburb. The comparative data will be taken from the 2024 AEDC results. The two timepoints will be analysed to see if there has been a significant decrease in the proportion of children in the ‘developmentally vulnerable in one or more domains’ category, as well as across all five EDI domains. The 2021 census data will not be used in this study due to disruptions to service delivery in 2020. Additionally, the interventions will have been running for less than a year at the time of the data collection, and therefore not enough dose will have been given to result in any significant impact on AEDC scores.

*Outcome measures*. Every three years the Early Development Instrument of the AEDC measures the five domains of early development described above in Australian children who are commencing their first year of full-time school. Under each of these domains, children are classified into one of three categories: developmentally on track, developmentally at risk and developmentally vulnerable. Summary indicators are then calculated for each community based on the proportions of children in each of these three categories. The primary focus for this study will be to reduce the proportion of children in the intervention community who are classified as developmentally vulnerable on one or more domains. We will also perform separate tests for significant change in the percentage of children at risk in each of the five individual EDIs.

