*Sample size estimates*. Our sample size calculation is based on the AEDC ‘critical difference estimates for communities’ [17]. We will focus the intervention on those suburbs (SA2) in the two poorest performing districts with the highest proportions of children with at least one EDI domain in the developmentally vulnerable category at the most recent census. For example, based on 2018 census results, ~40% of this sample have been classified as developmentally ‘at risk’, i.e. falling significantly behind their peers, and could benefit from early intervention. We anticipate that approximately half of this number, ~250–300 children, will be required to show a statistically significant difference. Our primary focus will be on reducing the number of children who are developmentally vulnerable on at least one index (Table 1). We will also perform separate tests for change in the percentage of children at risk in each of the five EDIs.

**Table 1 pone.0267666.t001:** Critical differences (%) to establish significant change for each of the six early development indices.

Community size (# of children)	Developmentally vulnerable (1+) (%)	Physical Health & wellbeing (%)	Social competence (%)	Emotional maturity (%)	Language & cognitive skills (%)	Communication & general knowledge (%)
200–299	4.7	5	4.6	4.9	4.8	5.2

Time-point comparisons will be made between 2021 and 2024 AEDC indices for both intervention and comparator areas. Across-area comparisons will be made between intervention and comparator areas for the 2024 census indices.

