#### Quantitative analysis

Testing for statistically significant differences in children’s early development indices will be based on the critical difference approach developed for the AEDC by Gregory and Brinkman [17]. The Gregory and Brinkman report provides the technical details to determine “how big” a difference (%) needs to be in the EDI results between two different time points or two different areas to be considered statistically significant [11, Tables 14 –primary outcome and 13 –the five secondary outcomes, respectively]. The method allows for the expected sample to sample variation and typical measurement error associated with the sort of data collected in the AEDC. Current versions of the methodology allow us to compare two point-estimates, either across time or between neighbourhoods, of the selected index. Table 1 shows the critical differences that will be needed to establish a significant change for each of the six EDI indices,—the primary outcome and five secondary outcomes—to be considered in this study. The population of children in the intervention and control areas is expected to be in the range 200–299 at the 2024 census. Time-point comparisons will be made between 2021 and 2024 AEDC indices for both intervention and comparator areas. Across-area comparisons will be made between intervention and comparator areas for the 2024 census indices. The following hypotheses will be tested for each of the six indices to be used in this study:

Each EDI for the intervention suburbs (within the Belconnen district) for the 2024 census will be significantly lower, i.e. show a significant reduction in the proportion of children who are developmentally vulnerable or at risk, compared to that in the control suburbs (within the Tuggeranong district)Each EDI for the intervention suburbs (within the Belconnen district) for the 2024 census will be significantly lower, i.e. show a significant reduction in the proportion of children who are developmentally vulnerable or at risk, compared to the corresponding value in the 2021 census

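### The five secondary domain outcomes are defined in conflicting ways, and the percentage 'at risk' can rise when children improve

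*Protocol article*

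**What the plan says.** The protocol article, under Developmental vulnerability (Outcome measures), sets out the classification: in each domain "children are classified into one of three categories: developmentally on track, developmentally at risk and developmentally vulnerable". The three categories are ordered and exclusive. The primary focus is then to "reduce the proportion of children in the intervention community who are classified as developmentally vulnerable on one or more domains".

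The five domain outcomes are described in three ways:

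- **At risk.** Outcome measures: "We will also perform separate tests for significant change in the percentage of children at risk in each of the five individual EDIs". Likewise, under Sample size estimates: "We will also perform separate tests for change in the percentage of children at risk in each of the five EDIs". The abstract plans tests for "significant differences in the percentage of children at risk in each of the five individual EDI domains".
- **Vulnerable.** The opening paragraph of Developmental vulnerability looks for a decrease in the vulnerable proportion "as well as across all five EDI domains".
- **Vulnerable or at risk.** Both hypotheses under Quantitative analysis, which apply to all six indices, "show a significant reduction in the proportion of children who are developmentally vulnerable or at risk".

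Research question 1, in the Introduction, asks whether the programme will "reduce the proportion of children who are considered developmentally at risk in the intervention community".

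**The concern.** The three descriptions lead to different counts from the same census table, so the secondary results depend on which sentence the analyst follows. Nothing in the article says that 'at risk' is shorthand for one of the others.

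The version stated most often is also the weakest. A middle category gains children from below and loses them to above, so its size can go either way when development improves. A domain in which the programme moved children out of the vulnerable category could show no change, or a significant change in the wrong direction. AEDC results are released as area proportions. If the category is still open when the 2024 figures appear, the choice could follow the result.

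**Working it through.** The article gives no figure for this point to reproduce, so the check is on how each definition responds to improvement.

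**Inputs**

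- V = vulnerable, A = at risk, T = on track (Outcome measures).
- Table 1 critical differences for a community of 200–299 children: physical 5, social 4.6, emotional 4.9, language 4.8, communication 5.2 percentage points. The domain columns name no category. Applying them to each candidate definition is an assumption.
- The sizes of the shifts are assumed. The article gives no domain-level baselines, and none are needed, because the changes do not depend on them.

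**Formulas.** Let a, b and c be the net percentage points shifting V to A, A to T and V to T. Each census measures a new school-entry cohort, so these are shifts in the distribution and not tracked children. The same algebra covers the area comparison.

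- Change in V = −a − c
- Change in A = a − b
- Change in V or A = −b − c

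With a, b and c all zero or positive, every shift is an improvement. V and 'V or A' can then only fall or stay level. A rises whenever a is greater than b.

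**Results with c = 0**

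| a (V to A) | b (A to T) | Change in V | Change in A | Change in V or A |
|---|---|---|---|---|
| 5 | 0 | −5 | +5 | 0 |
| 5 | 2 | −5 | +3 | −2 |
| 5 | 5 | −5 | 0 | −5 |
| 0 | 5 | 0 | −5 | −5 |

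For example, with assumed baselines V = 10% and A = 15%, the first row gives V = 10 − 5 = 5%, A = 15 + 5 = 20%, and V or A still 25%.

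**Against Table 1.** A change of 5 points reaches the threshold in four domains (5, 4.6, 4.9, 4.8) and falls short in communication (5.2). It equals the physical threshold exactly, so the count is three if the threshold must be exceeded.

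- First row: vulnerability falls significantly in four domains, the percentage at risk rises significantly in the same four, and the combined measure shows nothing.
- Second row: the same fall in vulnerability comes with +3 at risk and −2 combined. Both are below every domain threshold, so a benefit is hidden.
- Third row: the percentage at risk does not change at all.
- Fourth row: the percentage at risk falls by 5 and vulnerability does not change. The at-risk measure can therefore point the right way, but only when movement to on track dominates.

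**The case against.** **Loose usage.** Sample size estimates puts 'at risk' in inverted commas and explains it as lagging behind peers, straight after discussing vulnerability. That suggests the term is used informally for 'vulnerable'. It may well be the intent, but the article does not say so. Outcome measures names 'at risk' as a separate category in the same paragraph that states the test, and the hypotheses join the two terms with 'or'. Even if shorthand was meant, an analyst following the text would take the wrong AEDC column.

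**The hypotheses read item by item.** The wording could mean vulnerable for the primary and at risk for the domains. That is a fair reading. It removes the third definition and the mismatch with the primary in the hypotheses. It leaves the domains on the measure that can move the wrong way, and it still conflicts with the planned decrease in vulnerability across domains.

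**An analysis plan would settle it.** The problem is not missing detail. The article states conflicting definitions, and any later plan would have to overrule one of them.

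**Stronger readings that the article does not support**

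- A reader might infer that the primary outcome itself is undefined. It is not. The abstract, Outcome measures, Sample size estimates and the first column of Table 1 all use vulnerability on at least one domain or index. The mismatch is confined to research question 1 and the hypotheses.
- A reader might take 26.4% vulnerable and about 40% 'at risk' as measuring the gap between definitions. The first describes the whole Belconnen district and the second describes suburbs chosen for high vulnerability. A higher figure would be expected under a single definition.
- A reader might infer that a working programme will reverse all five secondary tests. A significant reversal needs a net a − b of about 5 points, and 5 points is not enough in communication.

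**Conclusion.** The point holds for the five secondary outcomes. Their definition is inconsistent, and the percentage at risk does not move in one direction with benefit. That second part follows from the article's own classification and needs no assumed baseline. In size, the same 5-point fall in vulnerability can come with a change of +5, +3 or 0 in the percentage at risk, and 0, −2 or −5 in the combined percentage. The +5 case reaches the Table 1 threshold in four of five domains, if those thresholds apply to that category, which the article does not show. The likelier harm is a hidden benefit. A significant adverse reading is possible but requires little onward movement to on track.

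For the primary outcome, the definition stands and only the surrounding wording needs correcting.

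**What to change.** Before the 2024 data are seen:

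1. Define each of the five secondary outcomes as the percentage developmentally vulnerable in that domain, matching the primary.
2. If the middle category is of interest, report the combined percentage vulnerable or at risk, labelled exploratory. It cannot rise when every shift is an improvement.
3. Align the abstract, research question 1, the opening, Outcome measures and Sample size paragraphs of Developmental vulnerability, and both hypotheses.
4. Confirm from the cited AEDC critical-difference report that the Table 1 domain values apply to the vulnerable category, and name the category in the column headings.

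Items 1 to 3 cost only wording and need no extra data. Item 4 needs a check of the source and, if the values belong to another category, replacement of the five domain thresholds.

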Over the last three censuses (2012–2018), the Australian Capital Territory (ACT) has seen an increase in the proportion of children who are developmentally vulnerable on all but one of the AEDC domains and the two summary domains, vulnerable on one or more domains and vulnerable on two or more domains [10]. As a result, early childhood development has been a focus recently in the ACT. Early investigations have shown that services, organisations, and sectors continue to operate in isolation, and, as a result, it has been reported that families struggle to access cohesive and holistic pathways of care for their children. Examining the variation in early childhood vulnerability across suburbs making up the ACT’s nine districts reveals greater developmental vulnerability is experienced in clusters of suburbs. According to the 2018 AEDC, 26.4% of 5-year-old children in the Belconnen district were developmentally vulnerable in one or more domains [11].

An inventory of all early childhood services in the Belconnen district in 2019 revealed that there were multiple services across the education, health, and social services sectors in operation. These included but were not limited to Early Childhood Education and Care (ECEC) services, playgroups, preschools and parenting programs. However, evidence suggests that vulnerable families are unable to or choose not to access these services, or are not aware of them [12]. The fragmented nature of service delivery and accessibility, particularly across centres and services, hinders referrals and restricts pathways of care for children with developmental needs. Under these conditions developmental issues are not addressed, while the number of children entering school with significant social, communication, behaviour and health challenges continues to increase. Research confirmed that when such challenges are present on entering formal education, there are cascading effects throughout the school years and later in life [3, 4]. These children are more likely to experience poor academic achievement, early drop-out from school and unemployment [13].

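### For the primary index, the 4.7-point critical difference does not cover ordinary sampling variation between two cohorts of 200–299 children, so each of the two primary comparisons would credit an ineffective programme about 9–14% of the time

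*Protocol article*

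**What the plan says.** The sample size paragraph of the protocol article (Developmental vulnerability) rests on published AEDC critical differences and reproduces one row of them in Table 1, captioned "Critical differences (%) to establish significant change for each of the six early development indices". For 200–299 children the entry for the primary index is 4.7 points. The five domain entries run from 4.6 to 5.2.

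The Quantitative analysis section makes this the test: "Current versions of the methodology allow us to compare two point-estimates, either across time or between neighbourhoods, of the selected index". It states what the cut-off covers: "The method allows for the expected sample to sample variation and typical measurement error associated with the sort of data collected in the AEDC". It also fixes the size: "The population of children in the intervention and control areas is expected to be in the range 200–299 at the 2024 census".

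Two comparisons follow for each index: intervention against control area in 2024, and the intervention area in 2024 against an earlier census. Both hypotheses are directional: each index "will be significantly lower, i.e. show a significant reduction in the proportion of children who are developmentally vulnerable or at risk". The article gives no significance level and no derivation of 4.7. The only rate it gives for the primary index is in the Introduction: "26.4% of 5-year-old children in the Belconnen district were developmentally vulnerable in one or more domains".

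**The concern.** A critical difference that allows for sampling variation should be at least as large as the usual 5% limit for a difference between two independent groups of the stated size. With a rate near one quarter and a few hundred children per group, 4.7 points looks too small, even before the measurement error that the method is also said to include.

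At stake is the decision rule for the primary outcome. If the cut-off is too low, a difference that chance often produces will be reported as a significant reduction in vulnerability and credited to the programme. The sample size paragraph would also suggest that smaller differences can be established than is the case.

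**Working it through.** **Inputs**
- Cut-off c = 4.7 points (Table 1, primary index, 200–299 row).
- Children per group n = 200, 250, 299 (Quantitative analysis; 250 is the approximate midpoint). Read as the size of each area, because Table 1 is indexed by community size. The earlier cohort is assumed to be of similar size.
- Rate p = 26.4% in both groups (Introduction; a district figure, assumed to apply to both). Range tried: 20–40%.
- Two independent groups of different children, both carrying sampling error; children treated as independent.

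**Formulas**
- SE = √(2p(1−p)/n)
- 5% limit = 1.96 × SE two-sided, 1.645 × SE one-sided
- Chance of a false benefit = 1 − Φ(c/SE), checked by exact summation over two binomials

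**Step 1: try to reproduce 4.7.** At p = 0.264 and n = 250, SE = √(2 × 0.264 × 0.736 / 250) = 0.0394, or 3.94 points.
- Two-sided 5%: 1.96 × 3.94 = 7.7 points.
- One-sided 5%: 1.645 × 3.94 = 6.5 points.
- One-sided 10%: 1.282 × 3.94 ≈ 5.05 points.
- One-sample, one-sided 5%: 1.645 × √(0.264 × 0.736 / 250) = 4.6 points. This is close to 4.7 but treats the second group as known without error, which does not fit a comparison of two point-estimates.

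No two-sample 5% limit gives 4.7 at this size and rate.

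**Step 2: the range of sizes at 26.4%**

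| n per group | SE (points) | two-sided 5% limit | one-sided 5% limit | 4.7 in SEs | false benefit, normal | false benefit, exact |
|---|---|---|---|---|---|---|
| 200 | 4.41 | 8.6 | 7.3 | 1.07 | 14.3% | 14.1% |
| 250 | 3.94 | 7.7 | 6.5 | 1.19 | 11.7% | 12.2% |
| 299 | 3.61 | 7.1 | 5.9 | 1.30 | 9.6% | 8.9% |

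**Step 3: other rates.** Over p = 20–40% and n = 200–299 the false-benefit chance is 7.5–16.9% by the normal approximation and 6.9–16.6% exactly. It is above 5% throughout.

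**Step 4: what 4.7 would require.**
- At 26.4%, n = 2 × 0.264 × 0.736 × (1.96/0.047)² ≈ 676 per group two-sided, or about 476 one-sided (1.645 in place of 1.96).
- At 200–299 per group, a rate of about 6–9.5% two-sided, or 9–14% one-sided.

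**Step 5: threshold against detectable effect.** A true difference equal to the significance threshold is detected only about half the time. For 80% power at two-sided 5%, the true difference must be roughly (1.96 + 0.84) × SE: 2.8 × 3.61 ≈ 10 points at n = 299 and 2.8 × 4.41 ≈ 12 points at n = 200.

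**The case against.** **The source is not shown.** The value comes from a cited technical report whose error model is not in the article. This stands as a limit on the diagnosis: a transcription slip, a wrong row and a different model cannot be told apart, and a reader should not infer that the report is wrong. It does not rescue the rule, because the article itself says sampling variation is covered.

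**A census has no sampling error.** The article claims the opposite about its method. The compared cohorts also contain different children, so chance variation between them has to be allowed for before a difference is credited to the programme.

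**The groups may be larger.** The sample size paragraph speaks of about half of an unstated number, roughly 250–300 children, which could imply 500–600. At 26.4% the one-sided error would then be 4.6% (n = 500) or 3.2% (n = 600) per area. The ambiguity is real, but the Quantitative analysis section and the chosen Table 1 row both state 200–299.

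**Stronger readings that the article does not support**
- *All six tests are too lenient.* Domain rates are not given. At assumed rates of 8–12% and n = 250, the domain cut-offs give about 1.6–6%.
- *Table 1 contradicts itself because the primary cut-off is below four of the five domain cut-offs.* This needs the domain columns to be subsets of the primary index. The domain tests are described as concerning children at risk, or vulnerable or at risk. The primary and domain values come from different source tables, and measurement error may differ by domain.
- *The primary rate in the target suburbs is 40%.* The article says "based on 2018 census results, ~40% of this sample have been classified as developmentally" at risk, a different category. Here it serves only as an upper sensitivity value.
- *The error rate is 23%.* That counts differences in either direction at n = 250; the stated hypotheses go one way.

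**Conclusion.** The point holds for the two primary-index comparisons, between areas and over time. At 26.4% and 200–299 children per group, 4.7 points is 1.1–1.3 standard errors. That is more than one standard error but well below any conventional 5% limit. The chance of declaring an ineffective programme beneficial is about 9–14% in each comparison, about 12% at 250 per group, and 7–17% if the rate lies anywhere in 20–40%.

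This rests on a common rate taken from the district figure, equal group sizes and independent children. Measurement error is left out, and positive clustering by suburb, school or teacher would raise the error further. The calculation shows that the cut-off does not do what the article says it does at this size and rate; it does not show why. Because the figure is the significance rule for the primary outcome, it should be corrected before the 2024 data are analysed.

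**What to change.** 1. Check the primary entry in Table 1 against its source column and community-size row, and state the confidence level it is meant to carry.
2. Do not use 4.7 points as the significance rule at 200–299 children. Decide both primary comparisons from the difference in percentages with a 95% confidence interval computed from the actual numbers of children, and call a difference significant only if the interval excludes zero. State that this is a minimum allowance, since it leaves out measurement error and clustering.
3. Keep the AEDC critical difference as a descriptive comparison.
4. Restate Table 1 and the sample size paragraph: the smallest observed difference reaching two-sided 5% significance is about 7–9 points at 26.4%. Label it a significance threshold, and say that 80% power would need a true difference of roughly 10–12 points. Make the expected number of children per area unambiguous in the same paragraph.

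The cost is a revised table, some analysis wording and a less favourable stated figure. No new data are needed.
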